#### Primary definition of disabling disease

The primary definition of disabling disease will be a modified version of that described by Beaugerie *et al*.^38^ The original definition has been modified to clarify some of the symptoms and to permit the use of disease-modifying therapy, since this has become a common preventative measure in modern practice. Disabling disease will therefore be defined as any of the following:

Hospitalisation after CD diagnosis for flare or disease complication, as judged by the treating clinician.More than two corticosteroid courses required over 5 years and/or dependence on corticosteroids.Any intestinal resection >50 cm, or surgical operation for perianal disease (examination under anaesthesia without seton placement does not meet this criterion; abscess drainage and/or seton placement does).Chronic disabling symptoms, defined as a cumulative time of over 12 months of one or more of the following:Diarrhoea with nocturnal stool (getting up for a bowel movement after having gone to bed).Urgency (defined as having to rush to the toilet for a bowel movement).Abdominal pain due to intestinal obstruction (requires imaging confirmation or surgical proof).Fever (documented tympanic temperature of >38.0°C or oral temperature of>38.3°C).Fatigue.Joint pain not due to an alternative cause.Uveitis.Pyoderma gangrenosum.

#### Alternative definitions of disabling disease

Since the Beaugerie criteria are imperfect, further definitions of adverse outcomes will also be collected; specifically the Liège criteria^37^ and Montreal behaviour criteria.^39^

The Liège criteria are met if any of the following occur:

Development of complex perianal disease.Any colonic resection.Two or more SB resections.A single SB resection of >50 cm.Definitive stoma.

Complex perianal disease is defined as per the American Gastroenterological Association,^40^ and the perianal disease modifier will be collected.

The Montreal behaviour criteria classify CD as either inflammatory (B1), stricturing (B2) or penetrating (B3). Stricturing disease will be defined as a fixed luminal narrowing of >50% relative to normal proximal bowel. Penetrating disease will be defined as an intra-abdominal or enterocutaneous fistula, inflammatory mass, or abscess.

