#### Consensus panel assessment of disease severity

Consensus panels will be convened at each recruitment sites. Panels will comprise, as a minimum, one gastroenterologist and one radiologist, aided by the site research nurse. The consensus panels will review all available clinical information. This will include investigations such as CRP, faecal calprotectin, endoscopy (conventional and capsule), imaging (MRI, US, CT and fluoroscopy), surgical and histopathological findings, clinical activity scores (eg, Harvey-Bradshaw Index) and overall clinical course including outpatient and inpatient clinical records.

Using all the available data, the consensus panels will record the presence or absence of disabling disease, and Montreal classification according to the protocol definitions and the date at which this endpoint was reached.

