#### Secondary outcomes

Comparative predictive ability of prognostic models incorporating MRE severity scores (MEGS, sMaRIA and Lémann index) versus models using standard characteristics alone to predict the development of Montreal B2 / B3 disease or Liège severe disease at 5 year follow-up.Identification of the best combination of individual MRE features to predict disabling CD within 5 years of new diagnosis.Average per-patient and national healthcare costs incurred within 5 years of new diagnosis.Patient, disease phenotype and imaging characteristics associated with higher economic costs within 5 years of diagnosis.

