### Retention

Participants need not undergo additional testing to enter this study. Only data obtained during routine clinical care are necessary to both define disabling disease and provide variables for model inclusion. Where participants are lost to local follow-up, participants’ general practitioner will be contacted to obtain routine clinical information, post consent (this is only applicable to METRIC cohort and those patients on retrospective cohort who have provided consent).

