#### Health economic analysis

To estimate mean 5-year costs per patient, we require NHS hospital resource use data for all patients accumulated during the follow-up period. These will be collected in a similar manner to the METRIC study, which captured similar costs but only for a 6-month time horizon. A study-specific CRF will capture hospital resource use data for the following cost components for each patient during follow-up: all imaging investigations; endoscopy; surgery; outpatient visits; inpatient stays; day cases and medications. These will be populated at each site by the relevant research team. Unit costs will be obtained from standard published sources, including NHS tariffs.

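### Montreal B2/B3 is ascertained only through routine-care examinations, so if patients with worse baseline MRE are re-examined more often, the added value of MRE for this secondary outcome can be overstated

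*Protocol article*

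**What the plan says.** Under Alternative definitions of disabling disease, B2 is set by a degree of narrowing: "Stricturing disease will be defined as a fixed luminal narrowing of >50% relative to normal proximal bowel". B3 is set by lesion type: "Penetrating disease will be defined as an intra-abdominal or enterocutaneous fistula, inflammatory mass, or abscess".

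Under Retention, the article states "Participants need not undergo additional testing to enter this study" and "Only data obtained during routine clinical care are necessary to both define disabling disease and provide variables for model inclusion". Time point of follow-up gives a minimum duration of 4 years but no examination time points.

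Under Consensus panel assessment of disease severity, "The consensus panels will review all available clinical information", and they record "Montreal classification according to the protocol definitions and the date at which this endpoint was reached". No category is described for a patient whose bowel was not examined again. Interpretation and blinding covers the radiologists who score the baseline MRE; nothing is said about blinding the panels to that scan.

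The endpoint is used to compare models with and without MRE scores "to predict the development of Montreal B2 / B3 disease or Liège severe disease at 5 year follow-up". Statistical methods, secondary outcome 1, applies the primary-outcome modelling to it, provided that events and non-events are adequate; otherwise the results are descriptive. Multiple imputation is stated for covariates only.

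**The concern.** Every patient has an MRE at diagnosis. Later, B2 and most B3 lesions come to light only in patients who are examined. If the chance of being examined rises with baseline MRE severity, the chance of recording the outcome depends on the predictor under test. MRE scores could then appear to improve prediction of B2/B3 partly because high scorers are looked at more, and the error would favour the study hypothesis. Bootstrap internal validation would not reveal it, because every resample carries the same misclassification. The 5-year incidence of B2/B3 would also be understated.

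More is at stake here than for the other alternative endpoint. Liège severe disease is expected to be descriptive only, at about 41 events. No such expectation is stated for B2/B3, so it is the likelier of the two to be modelled and reported in support of MRE.

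**Working it through.** **The plan's own figures.** 207 × 0.55 = 113.9 and 207 × 0.60 = 124.2 events; 207 − 113.9 = 93.1 and 207 − 124.2 = 82.8 non-events; Liège 207 × 0.20 = 41.4. These match the stated 114–124, 83–93 and 41. No incidence is given for B2/B3 and no re-examination rate is given, so everything below rests on assumptions.

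**Inputs.** N = 207 comes from Sample size and justification. The following are assumed:
- the true 5-year B2/B3 incidence *p* is the same in the upper and lower halves of the baseline MRE score, so there is no true association;
- a share *s* of true cases is silent and is found only on re-examination;
- the re-examined proportion *r* differs between the halves.

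**Formulas.** Observed incidence = *p* × (1 − *s* + *s* × *r*). The spurious odds ratio is the ratio of the two observed odds. Missed cases = 207 × (*p* − mean observed incidence).

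**Central illustration** (*p* = 30%, *s* = 50%, *r* = 90% against 50%):
- High half: 0.30 × (0.5 + 0.5 × 0.9) = 28.5%.
- Low half: 0.30 × (0.5 + 0.5 × 0.5) = 22.5%.
- Odds ratio: (0.285/0.715) / (0.225/0.775) = 1.37.
- Missed: 207 × (0.300 − 0.255) = 9.3 of 62.1 true cases.

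**Range:**

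| *p* | *s* | *r*, high vs low | Observed incidence | Odds ratio |
|---|---|---|---|---|
| 20% | 30% | 90% vs 70% | 19.4% vs 18.2% | 1.08 |
| 30% | 50% | 90% vs 70% | 28.5% vs 25.5% | 1.16 |
| 30% | 50% | 90% vs 50% | 28.5% vs 22.5% | 1.37 |
| 40% | 50% | 90% vs 50% | 38.0% vs 30.0% | 1.43 |

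**What this would do to the planned comparison.** Take a single high/low predictor with 103 and 104 patients per half. BIC favours adding it when the likelihood-ratio statistic exceeds ln 207 = 5.33. With binomial sampling, the central illustration gives an AUC of 0.54, a likelihood-ratio test significant at 5% in about 17% of studies, and BIC preferring MRE in just under 10%. The 90% against 70% case at *p* = 30% gives an AUC of 0.52 and BIC preferring MRE in about 4%. The last row of the table gives about 14%. With equal re-examination in both halves the odds ratio is 1.0, and BIC wrongly prefers MRE in about 2%.

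Larger gaps do more. If 90% of all true cases are detected in the high half and 50% in the low half, the odds ratio is 1.98 to 2.25 for *p* of 20% to 40%. That is harsher than the central illustration, where detection is 0.5 + 0.5 × 0.9 = 95% against 0.5 + 0.5 × 0.5 = 75%, so it is not used for the conclusion.

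**The case against.** The strongest reply has five parts.

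- **The link is inferred.** Nothing in the article says that re-examination depends on baseline MRE severity. Routine-care imaging at diagnosis is stated for the retrospective cohort; METRIC patients, 131 of 207 (63%), had their MRE within that trial. This stands: the link is plausible, because radiological findings form part of the diagnosis in both cohorts, but it is not documented.
- **The panels may not default to non-progression.** A reader might infer that any patient not re-imaged is counted as not progressed. The article does not say so; it gives no rule for such patients. Nor is the whole endpoint a luminal measurement: that applies to B2 only, and an enterocutaneous fistula can be seen clinically. Symptomatic strictures would usually be investigated, so the problem lies mainly with subclinical disease.
- **The size is modest and unadjusted.** The real comparison adds MRE to a baseline model that already holds stricturing, perianal and severe endoscopic disease, location, CRP and calprotectin. To the extent that these also drive re-examination, the spurious increment would be smaller. This stands.
- **The consequence is limited.** The outcome is secondary and modelled only if events are adequate. The primary definition rests mainly on hospitalisation, steroids, surgery and symptoms. This stands and sets the weight of the point.
- **This belongs in the SAP.** A sensitivity analysis may well be specified there. But the protocol itself fixes an examination-dependent outcome, routine-care ascertainment and modelling carried over from the primary outcome. Followed as written, that combination can bias the comparison, so the point is more than a missing detail.

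**Conclusion.** The concern holds in conditional form and is minor. B2 and most B3 lesions need an examination to be recorded, ascertainment is left to routine care, and the resulting endpoint is used to test baseline MRE. If re-examination is more frequent in patients with worse baseline MRE, the added value of MRE for B2/B3 can be overstated. With no true association, incidence of 20–40%, a silent share of 30–50% and re-examination gaps of 20–40 percentage points, the spurious odds ratio is about 1.1 to 1.4, unadjusted for the baseline model. All of these inputs are assumptions; the documents supply none of them, so the actual bias cannot be calculated.

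A reader might go further and conclude that the B2/B3 comparison is biased, or that the primary result is compromised. The documents support neither reading.

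**What to change.** 1. Tabulate post-baseline bowel imaging and endoscopy per patient-year by baseline MRE score. The panels already review these investigations, and the resource-use CRF covers "all imaging investigations; endoscopy; surgery; outpatient visits; inpatient stays; day cases and medications". The article does not say that the CRF holds dates, so record them where they are not already held.
2. Prespecify a sensitivity analysis of the B2/B3 models that counts only clinically presenting events: admission, drainage, dilatation or surgery for obstruction, abscess or fistula. Detection of these depends much less on elective re-examination.
3. Qualify any B2/B3 conclusion that is not consistent with that analysis in direction and size.
4. Do not make censoring at the last informative examination the main analysis. If well patients are examined less, it would remove their event-free time, and the censoring would itself be informative.

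The cost is some SAP wording and a link between examination records and the outcome file, with no new tests and no change to care. The downside is fewer events and lower precision in the sensitivity analysis. This is a cheap improvement.

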#### Consensus panel assessment of disease severity

Consensus panels will be convened at each recruitment sites. Panels will comprise, as a minimum, one gastroenterologist and one radiologist, aided by the site research nurse. The consensus panels will review all available clinical information. This will include investigations such as CRP, faecal calprotectin, endoscopy (conventional and capsule), imaging (MRI, US, CT and fluoroscopy), surgical and histopathological findings, clinical activity scores (eg, Harvey-Bradshaw Index) and overall clinical course including outpatient and inpatient clinical records.

Using all the available data, the consensus panels will record the presence or absence of disabling disease, and Montreal classification according to the protocol definitions and the date at which this endpoint was reached.

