#### Interpretation and blinding

MRE scans will be interpreted by one from a pool of recruitment site radiologists; all are GI radiologists and experienced in MRE, in both clinical and research settings. Radiologists will be allocated MRE scans for scoring. These will be interpreted blinded to all clinical information other than that relevant for the calculation of the relevant index (eg, surgical history for LI).

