### Outcomes

#### Primary outcome

Comparative predictive ability of prognostic models incorporating MRE severity scores (MEGS, sMaRIA and Lémann index) versus models using standard characteristics alone to predict disabling CD (modified Beaugerie definition) within 5 years of new diagnosis.

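### Site panels decide the primary endpoint with the baseline MRE in view, so knowledge of the predictor under test can influence the outcome; the article blinds only the MRE score readers

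*Protocol article*

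**What the plan says.** Under Consensus panel assessment of disease severity, the article places the outcome decision locally: "Consensus panels will be convened at each recruitment sites". On membership: "Panels will comprise, as a minimum, one gastroenterologist and one radiologist, aided by the site research nurse". On the evidence: "The consensus panels will review all available clinical information". The list that follows includes "imaging (MRI, US, CT and fluoroscopy", along with CRP, faecal calprotectin, endoscopy and the clinical records. On the decision: "Using all the available data, the consensus panels will record the presence or absence of disabling disease". The panel also records the Montreal class and the date on which the endpoint was reached.

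Under Interpretation and blinding, the article says who produces the predictors: "MRE scans will be interpreted by one from a pool of recruitment site radiologists". It then blinds those readers: "These will be interpreted blinded to all clinical information other than that relevant for the calculation of the relevant index".

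The primary outcome is "Comparative predictive ability of prognostic models incorporating MRE severity scores (MEGS, sMaRIA and Lémann index) versus models using standard characteristics alone", for disabling disease by the modified Beaugerie definition within 5 years.

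**The concern.** Blinding is stated in one direction. The MRE scores are protected from knowledge of the clinical course, but the judgement of the clinical course is not protected from knowledge of the MRE. In a study of the added prognostic value of one test, the outcome assessor should not know that test's result.

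If a panel knows that the diagnostic scan showed extensive disease, a borderline case (were there really 12 months of fatigue or urgency, was the patient truly steroid-dependent?) can be settled in line with the scan. The recorded outcome then contains some of the predictor. Internal validation does not help, because bootstrap samples are drawn from the same adjudicated outcomes and carry the same error. A biased endpoint date would also affect the planned 1-, 2- and 3-year predictions.

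The same radiologist could also hold both roles. Scorers are recruitment-site radiologists, each panel sits at a recruitment site and includes a radiologist, and the article does not separate the two.

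**Working it through.** This point concerns who sees what, so the main check is a comparison of sections. The arithmetic in steps 4 and 5 is illustrative.

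1. **Is the baseline MRE in the panel's material?** Study design says all METRIC patients had MRE. Eligibility criteria says the retrospective cohort had it in routine care at diagnosis. The panel's remit covers all available information and names MRI without limiting it to follow-up scans. So the baseline scan or its report is in view. The article does not say that panels see the MEGS, sMaRIA or Lémann scores.

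2. **Does any section withhold it?** No. The blinding statement applies to score readers only. This is a stated procedure and not a detail left out: an instruction to use everything available conflicts with holding one item back.

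3. **Which components depend on the panel's judgement?** From Primary definition of disabling disease:

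| Component | Main source of the decision |
|---|---|
| Hospitalisation for flare or complication | Treating clinician's attribution |
| More than two steroid courses | Record |
| Steroid dependence | Panel judgement |
| Resection over 50 cm, perianal surgery | Record |
| Over 12 cumulative months of urgency, fatigue, joint pain and similar | Panel judgement, mainly of duration |
| Obstructive pain | Imaging or surgical proof, plus duration |
| Date of endpoint | Panel |

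Any one component suffices, so a patient who clearly meets a record-based criterion cannot be reclassified through the judged ones, though the date may still move.

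4. **The plan's own event counts.** With N = 207 and prevalence 55% to 60%: events 207 × 0.55 = 113.9 and 207 × 0.60 = 124.2; non-events 207 × 0.40 = 82.8 and 207 × 0.45 = 93.2. These reproduce the stated 114–124 and 83–93. No figure in the article is disputed.

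5. **What leakage could do (assumed rates; the article gives none).** Assume prevalence 57%, a clinical score with c-index 0.70, and one MRE score with no true value. Let a share f of all outcomes be decided only by whether the MRE score exceeds its 43rd centile, which keeps prevalence at 57%. BIC prefers the model with one added score when the likelihood-ratio statistic exceeds ln(207) = 5.33. The probability of that comes from a chi-square distribution with 1 df, non-central when there is leakage. Odds ratios, c-indices and non-centrality come from a simulated population of 400,000, the last scaled to N = 207.

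| f | MRE odds ratio per SD | c-index, clinical alone → with MRE | Non-centrality | Chance BIC favours MRE |
|---|---|---|---|---|
| 0 | 1.00 | no true gain | 0 | 2% |
| 5% | 1.09 | 0.691 → 0.693 | 0.36 | 5% |
| 10% | 1.19 | 0.681 → 0.687 | 1.43 | 13% |
| 20% | 1.43 | 0.661 → 0.685 | 5.70 | 53% |

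Here f is a share of all outcomes. If 20% of outcomes were borderline (assumed), f = 5% means that a quarter of them follow the scan (0.20 × 0.25), f = 10% means half (0.20 × 0.50), and f = 20% means every one. The model leaves out any leakage from the standard predictors, so it shows one mechanism and not the net bias.

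**The case against.** The strongest reply is that little of this endpoint is open to influence. Steroid course counts, resection length and perianal surgery are in the record, obstruction needs proof, and the panel must apply the protocol's definitions. This stands. It limits the size of the problem, but steroid dependence, symptom duration and dating remain exposed.

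Four stronger readings are tempting, and the article does not support them.

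- A reader might infer that the same person scores and adjudicates a patient. The article allows this but does not say it. It does not say that scans are scored at the patient's own site, and the allocation rule may be in the full protocol. The leakage point does not need this limb.
- A reader might count hospitalisation among the panel's judgements. The definition gives that attribution to the treating clinician, and withholding a report from the panel would not change it.
- A reader might infer that the bias must favour MRE. Panels also see CRP, calprotectin and endoscopy, which overlap the standard model's predictors. The standard model can be inflated too, and the primary comparison is between the two models.
- A reader might put a large odds ratio on the effect. Take a median split at 58% prevalence and move 5% of all calls towards the scan: 0.58 + 0.05 × 0.42 = 0.601 against 0.58 − 0.05 × 0.58 = 0.551, odds ratio 1.23. At 10% it is 0.622 against 0.522, odds ratio 1.51. If only 20% of calls are borderline (assumed), moving 5% or 10% of those moves 1% or 2% of all calls: 0.584 against 0.574, odds ratio 1.04, and 0.588 against 0.568, odds ratio 1.09. The larger figures would require every call to be borderline.

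**Conclusion.** The concern holds in a limited form. As written, the panels decide disabling disease with the baseline MRE available to them, no blinding protects that decision, and nothing prevents a patient's MRE scorer from sitting on the panel. Knowledge of the scan can influence the judged components and the endpoint date, and so distort the estimated added value of MRE. Bootstrap validation would not show it.

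The size cannot be derived from the article. In the illustration the effect is small when 5% of all outcomes follow the scan and material only towards 20%, which would be extreme given how many components are record-based. The net direction is uncertain. The Montreal B2/B3 endpoint is secondary but more exposed, since stricture and fistula are themselves seen on imaging. Because protection is cheap, the change is worth making even though the bias may be modest.

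**What to change.** 1. For the modified Beaugerie and Liège decisions, give the panel a packet without the baseline MRE images, their report or any study scores. Follow-up imaging stays available, so later obstruction can still be confirmed.
2. Record and lock those decisions and dates before releasing the baseline scan for the imaging-based Montreal classification.
3. Do not allocate a patient's MRE for scoring to a radiologist on that patient's panel. Scans are already allocated from a pool, so only the allocation changes.
4. Prespecify a sensitivity analysis of the primary comparison limited to the objective components: steroid course count, resection length, perianal surgery and hospitalisation. Report its event and non-event counts, since the narrower outcome will have fewer events.

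Trial status gives a 2018 start and expected closure in late 2022 or early 2023, so some panels may already have met. For those patients the sensitivity analysis is the remedy, with the lack of panel blinding stated as a limitation.

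The cost is packet preparation at each site and a two-step panel decision, with no new tests and existing staff. Mentions of the baseline MRE may remain in clinic letters and inpatient notes, so blinding will be incomplete. The Montreal endpoint stays unprotected, and its results should be read with that in mind.
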